**Fig. 2 Fig2:**
[figure not shown]
Stepped-wedge cluster randomized trial plan

Data will be collected throughout the trial, which will allow us to compare the percentage of patients who have access to a fertility preservation consultation before and after the distribution of updated brochures and the awareness training of health professionals. This will allow us to assess the impact of these tools on the primary outcome measure.

### Setting

The study will be carried out in the Pays de la Loire and Occitanie regions, in accredited cancer centers.

### Participants

All oncologists practicing in accredited cancer centers will be invited to participate in the stepped-wedge cluster randomized trial. The managers of the RCNs involved in the project will liaise with health professionals in those cancer centers. In both regions 60 cancer licensed centers will be involved in our trial, 44 in Occitanie and 16 in Pays de la Loire. These centers will be classified in 6 randomization groups (clusters), and each cluster will have access to implemented information tools and newly created training resources for practitioners at different times as shown in Fig. 1.

#### Inclusion criteria for patients

We will include all women over 18 and under 40 years old, treated for a newly diagnosed breast cancer and receiving injectable chemotherapy in one of the participating centers.

#### Exclusion criteria for patients

There are no exclusion criteria.

### Data collection

As detailed in Fig. 3, we will collect patients’ age, date of diagnosis, cancer stage, and cancer center where the cancer has been diagnosed in the A-file, and type of chemotherapy start date, oncologist name, and cancer center where the patient will be treated in the B-file. Information regarding whether patients accessed a fertility preservation consultation and underwent fertility preservation will be provided by the electronic records of the assisted reproductive technology (ART) centers (File D). The number of cancers centers varies by region, requiring specific regional coordination for data collection. Data from files A, B and D can be queried directly and will not require ad hoc manual collection. On the other hand, additional data will be collected from patients’ medical records in the institutions (File E): number of children; address; presence or absence of information on fertility preservation; name of the oncologist.

**Fig. 3 Fig3:**
[figure not shown]
Data Architecture

### Participation and recruitment procedures for trial entry

In both regions, a Clinical Research Associate (CRA) will be responsible for collecting the data mentioned previously. This person will have access to the patients’ files and will be able to collect the necessary information. The data collected will only be stored on the servers of the RCNs that are authorized to store this type of information.

### Ethical approval, consent and recruitment strategies

The trial has received approval from the local research ethics committee (“Le Comité d’Ethique de la Recherche”) at the University of Toulouse III Paul Sabatier, France (ref 2023-609R2, dated 21st May 2023). According to French ethical regulations, as we are not modifying the care pathway and our trial is based on existing records, written or oral informed consent from patients is not required. However, following CPP (Comité de Protection des Personnes) recommendations a poster will be displayed in the health professional’s waiting room to inform patients that their personal data could be collected for our study, and the procedure for objecting will be clearly indicated. The same document will be given to patients or appended in their medical records.

### Outcome measures

#### Primary outcome measure

The primary outcome measure is the uptake rate of fertility preservation counselling for included patients.

### Secondary outcome measures

We will assess whether participants have undergone fertility preservation treatment, and which fertility treatment was chosen. Any traceable information related to the information given by doctors to patients on the fertility preservation process noted in the medical records will also be collected.

In addition, and as mentioned in the data collection section above, we will collect the following information: age, date of diagnosis, cancer stage and cancer center(s), type of chemotherapy treatment, chemotherapy start date, name of oncologist, number of children and patient’s address (for geocoding and determination of deprivation level using the European Deprivation Index). These data will be analysed in relation with the primary outcome.

### Sample size and power calculation

We will include all eligible patients over a period of 30 months starting 7 months before randomization of the first cluster and ending 7 months after randomization of the last cluster. This will allow us to reach a total sample of 750 included patients, based on a feasibility assessment of 2/3 of eligible patients recruited in the Occitanie region and 1/3 in the Pays de la Loire region. Assuming a proportion of access to fertility consultation of 23% before the intervention, with 6 clusters of about 120 patients and for an alpha risk of 5%, the smallest detectable effect of the intervention that we will be able to identify with 80% power will be 5.5% points. By knowing the date of the intervention and the date of the PCR, we will be able to identify whether patients were treated as part of usual care or in the intervention phase.

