In Europe, a Dutch retrospective study conducted at the Radboud University Medical Center found that only 9.8% of all eligible patients under the age of 40 and seen at a university hospital in 2011 were referred for fertility preservation counselling. In addition, this study found that referral to counselling was hampered by a lack of information about the services offered by fertility preservation centers, and by a lack of collaboration among healthcare providers [13]. In Denmark, a study conducted in 2023 among young women with cancer and informed of the risks to their fertility showed that their doctors’ choice of treatment was not in favour of preserving their fertility, as survival was more important [14]. In France, a lower rate of self-reported discussion of infertility risk (46%) was reported by the 102 of 1161 oncologists who responded to a national survey between 2012 and 2013. Moreover, only 22% of oncologists reported referring the patient to a fertility center before starting treatments [15]. More recently, the FEERIC study (FErtility, prEgnancy, contRaceptIon after breast Cancer in France) showed that around 46% of survey respondents were offered specialized oncofertility counselling [16].These results are all the more worrying considering that 80% of female respondents had a high level of education, with university degrees and therefore a high level of literacy.

French regional studies carried out in Occitanie (a region in the south-west France with a population of 6 million) have shown that only 23% of women under 40 treated with chemotherapy for breast cancer received an oncofertility consultation and 8.7% received fertility preservation between 2012 et 2017. Only 44% of oncologists were confident that ovarian stimulation treatment could be used, and 29% overestimated the time required for fertility preservation [17]. Information and access to an oncofertility consultation were influenced by the type of care structure, the woman’s age, her parity at the time of diagnosis, and the metastatic status of the cancer [18]. Furthermore, another regional study showed that if all women were informed of the risks of hypo fertility related to chemotherapy, then gamete preservation could be increased by 15.35% in women aged < 30 and 22.88% in women aged 30 to 35 [19].

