### Trial design

We will conduct a two-arm, multi-site, stepped-wedge cluster randomized trial in two participating French regions over a 30-months period (objective 2). Centers accredited to treat cancer will be grouped into 6 clusters to define the study sites depending on geographical position. The order in which these groups will have access to the intervention will be randomized. Depending on the stage at which a group is randomized, after a period of usual care of 7, 10, 13, 16, 19, or 22 months, the intervention will run for 22, 19, 16, 13, 10, or 7 months, respectively, in each group. We chose a stepped-wedge design to examine how the effect of the intervention evolves over time, to limit the risk of contamination within a site, and to ensure that the intervention is implemented in a way that maximizes adherence to optimal use, with 1-month training and transition period (see Fig. 2). Further, this type of trial ensures the access to the intervention for all participants. Eligible patients (*N*=750) seeing participating health professionals at these sites will be recruited.

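### The 5.5-point detectable effect at 80% power does not follow from the stated inputs: about 750 women give roughly 9 points in a plain two-sided comparison, and more once calendar time is adjusted for.

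*Protocol article*

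**What the plan says.** The inputs and the result are printed together under Sample size and power calculation in the protocol article.

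- Baseline: "Assuming a proportion of access to fertility consultation of 23% before the intervention". The value matches the regional figure in the Background, where "only 23% of women under 40 treated with chemotherapy for breast cancer received an oncofertility consultation".
- Size: "This will allow us to reach a total sample of 750 included patients", described as six clusters of about 120.
- Error rate: "for an alpha risk of 5" per cent. Whether the test is one- or two-sided is not said.
- Result: "the smallest detectable effect of the intervention that we will be able to identify with 80% power will be 5.5% points".

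Trial design gives the calendar. Over 30 months each cluster switches "after a period of usual care of 7, 10, 13, 16, 19, or 22 months". Intervention time mirrors this, from 22 months down to 7, with one transition month per cluster. Under the analyses for objective 2, the consultation rate is compared between the usual care and intervention phases, with clinician as a random effect and group as a fixed effect.

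**The concern.** A change from 23% to 28.5% is small for a binary outcome with about 375 women on each side, and 80% power for it looks too good even before clustering or calendar time is considered. This figure is the article's only statement of how sensitive the trial is on its primary outcome. If it is wrong, readers and funders are told that the trial can reliably detect a gain which it would in fact miss more often than not. A true gain of 5 to 10 points would probably be missed as well.

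**Working it through.** **Inputs.** From Sample size and power calculation: baseline p1 = 0.23, alpha 5%, power 80%, stated effect 0.055 (so p2 = 0.285), and N = 6 × 120 = 720, or 750 (125 per cluster). From Trial design: usual care 7 + 10 + 13 + 16 + 19 + 22 = 87 cluster-months, intervention also 87, transition 6, total 180. The two phases are therefore 1:1, and with 750 women each has 750 × 87/180 = 362.5 analysable women (725 in all).

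**Step 1: try to reproduce 5.5 points with a simple two-group comparison** (no clustering, no time effect).

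Required n per group = [z(0.975)·√(2p̄(1−p̄)) + z(0.80)·√(p1(1−p1) + p2(1−p2))]² / (p2−p1)², with p̄ = 0.2575.

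= [1.960 × 0.6184 + 0.842 × 0.6172]² / 0.055² = 2.998 / 0.003025 ≈ 991 per group, or 1,982 in total. One-sided, the same formula gives 781 per group.

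Power at 375 per group: SE = √[(0.1771 + 0.2038)/375] = 0.0319, so 0.055/0.0319 = 1.726.

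- Two-sided: Φ(1.726 − 1.960) = 41%
- One-sided: Φ(1.726 − 1.645) = 53%

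At 360 per group the corresponding powers are 39% and 52%.

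Solving for the difference that has 80% power:

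| Women per group | Two-sided | One-sided |
|---|---|---|
| 375 | 9.1 points | 8.1 points |
| 360 | 9.3 points | 8.2 points |

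Arcsine and constant-variance versions give 8.6 to 9.3 points two-sided. The 5.5-point figure is not reproduced.

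**Step 2: the stepped wedge on the protocol's calendar.** I used generalised least squares on the risk-difference scale, with outcome variance 0.23 × 0.77 = 0.1771, N = 750, the transition month dropped, random cluster effects, and seven periods of 7, 3, 3, 3, 3, 3 and 8 months. Detectable effect = (1.960 + 0.842) × SE = 2.802 × SE. ICC and cluster autocorrelation (CAC) are my assumptions.

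| Period effects | CAC | ICC | SE (points) | Detectable (points) | Power for 5.5 |
|---|---|---|---|---|---|
| yes | 1 | 0.01 | 5.64 | 15.8 | 16% |
| yes | 1 | 0.05 | 5.87 | 16.4 | 15% |
| yes | 1 | 0.10 | 5.79 | 16.2 | 16% |
| yes | 0.5 | 0.05 | 6.59 | 18.5 | 13% |
| yes | 0.5 | 0.10 | 7.43 | 20.8 | 11% |
| no | 1 | 0.01–0.10 | 3.15–3.23 | 8.8–9.0 | 40–41% |
| no | 0.5 | 0.01–0.10 | 3.35–4.61 | 9.4–12.9 | 22–37% |

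**Step 3: a more favourable simplification.** Seven equal periods with no transition month, 120/7 = 17.1 or 125/7 = 17.9 women per cluster-period, period effects, CAC 1 and ICC 0.01 to 0.10 give 13.2 to 14.5 points and power for 5.5 points of 19 to 21%.

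Steps 2 and 3 favour the plan in two ways: they hold the variance at its 23% value, although it is larger at 28.5%, and they use normal rather than small-sample critical values with only six clusters.

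**The case against.** The best defence is that the article condenses a fuller protocol and leaves out the ICC, the sidedness and the formula, any of which could change the answer. The missing ICC is indeed no finding in itself, because an article may leave it to the full document. But the inputs and the result are both printed, and no plausible choice of the unstated items reconciles them. One-sided testing still gives about 8 points. With 750 women and CAC 1, reaching 5.5 points two-sided would need an ICC of about 0.65 without period effects or about 0.90 with them, which is not plausible for this outcome.

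The defence does limit how far the point may be pushed. A reader might infer more in four respects:

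- *That no analysis could detect less than 9 points, or that 5.5 is strictly impossible.* Neither holds. The sidedness is unstated and a one-sided test gives about 8.1 points. Two-sided without period effects, the calendar gives 8.4 to 9.0 points at CAC 1 for an ICC of 0.01 to 0.20.
- *That clustering can only worsen the figure.* In a stepped wedge the detectable effect does not rise steadily with the ICC, because within-cluster comparison removes between-cluster variance. In the table it falls from 16.4 to 16.2 points between ICC 0.05 and 0.10.
- *That one narrow range is the true figure for this design.* It depends on correlations the article does not give and on whether calendar time is modelled. The objective 2 analysis names no calendar-time term.
- *That the cause is known.* Entering 120 women per cluster per period (6 × 7 × 120 = 5,040 women) gives about 5.5 to 5.7 points, but so does a one-sided, one-sample test of 360 to 375 women against a fixed 23%. The article supports neither route.

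Nor does the article say that a null result would be read as ruling out a 5.5-point gain. That is a risk for readers, not a claim in the plan.

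**Conclusion.** The statement is wrong as written. For a two-phase comparison of 720 to 750 women at a 23% baseline, the detectable effect is about 9.1 to 9.3 points two-sided (8.1 to 8.2 one-sided), and power for 5.5 points is about 40% (about 53% one-sided) instead of 80%. This rests only on figures printed in the article and on standard normal approximations.

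The design-specific figures are conditional on an assumed ICC of 0.01 to 0.10 and on period adjustment. They are about 16 points at cluster autocorrelation 1, up to about 21 at 0.5, and about 13 to 14.5 under seven equal periods, with power for 5.5 points of about 11 to 21%. Leaving calendar time out gives about 9 to 13 points over the same correlations, which still does not rescue the statement and leaves the effect confounded with any secular trend.

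**What to change.** Replace the 5.5-point statement with a recomputed detectable effect that uses:

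- about 120 to 125 women per cluster in total, that is about 17 to 18 per cluster-period on average;
- the actual step calendar, with the transition month handled as in the analysis;
- cluster and period effects;
- the sidedness of the test;
- a stated range of ICC and cluster autocorrelation, with the detectable effect shown across it.

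Report the resulting power for 5.5 points alongside, so that readers can see how the new figure relates to the published one. The cost is a recalculation and a change of wording. No extra patients are needed. The downside is a less favourable stated figure.

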### Randomization

#### Sequence generation, type of randomization and allocation concealment

We will use an R script from the R software [33] to perform the randomization of the six participating clusters. Randomization will take place at the start of the trial, to determine the order of participation in the intervention of each of the six clusters. Eligible patients of participating health professionals in each cluster will be a priori allocated to the usual care phase before the intervention or to the intervention phase after the intervention. The random allocation sequence will be concealed to health professionals until the beginning of the intervention for their cluster (Fig. 1). The random allocation sequence will likely remain concealed to patients.

#### Changes to intervention allocation

There are no established criteria for discontinuing or modifying the allocated intervention for study participants due to the low-risk nature of the study. However, each participating health professional will be asked to record the reasons if any for patient refusal to collect data and remain in the study.

### Blinding

Due to the nature of the trial and intervention delivery, health professionals will be aware of whether they are in the usual care or intervention phase of the trial (Fig. 1). Participants will likely not be aware of which phase of the trial they are in. However, we cannot guarantee the blinding of participants throughout the trial. The data analyst will be blinded to usual care or intervention phase allocation.

### Qualitative data

The improvement of information tools and create awareness training for health professionals (objective 1), will be carried out in two phases. The first phase will consist of focus groups or semi-structured interviews to review both existing brochures previously developed by the RCNs specialist groups. Focus groups will last up to one hour, and will be conducted by videoconference separating the two categories of stakeholders: healthcare professionals and patients. We will ask focus group participants to suggest modifications and content for health professionals’ awareness training. Each focus group will include up to 12 participants. The second phase will consist of semi-structured interviews with other healthcare professionals and patients to assess the acceptability, usability and feasibility of the modified tools in routine clinical practice, integrating the results of phase 1. We will recruit 6 to 12 participants per group (one group with health professionals and one group with patient and patient partners) or until thematic data saturation is reached [34].

## Data management and statistical analysis

### Data management

The data will be archived on the SYNERGIE secure platform at the University Toulouse III (UT3) and on the EPIDEMIO server at the IUCT Oncopole of Toulouse. Health professional consent forms will also be stored digitally in a dedicated folder on the UT3 secure platform. An anonymous participant ID number will be assigned to each eligible patient of the participating health professionals. A mapping table will be established and managed by the RCN team. This mapping table will be stored digitally in a dedicated folder on a secure platform. Only the RCN project leaders will have access to it.

### Analysis plan

To identify outliers and missing data, the initial examination of the data will include descriptive statistics, frequency distributions and histograms.

#### Analyses corresponding to objective 1

We will measure the usability, acceptability, and feasibility of the complex intervention and the newly developed training content. We will use the relevant domains of Morville’s “honeycomb” framework to test the usability and acceptability of the intervention elements (see Fig. 4) [35]. We will adapt relevant elements of the complex intervention to optimize their use in routine clinical settings.

**Fig. 4 Fig4:**
[figure not shown]
Morville’s “honeycomb” framework

We will use Morville’s “honeycomb” framework as an analytical lens to examine the data collected in relation to our hypothesis. Observations and field notes from interviews and focus group transcriptions will also be included in the analysis. Initial descriptive codes will be generated based on the Morville frame domains. Inductive coding will also be used to capture other naturally emerging themes. Categorical codes that combine the deductive and inductive codes will be developed in a third round of coding. Dual independent coding of 20% of all transcriptions will be conducted.

#### Analyses corresponding to objective 2

In response to our overall aim, we will compare the rate of fertility preservation counselling between the usual care phase and the intervention phase. We will use linear regression models as appropriate for the primary outcome measure. Because each group is exposed to the intervention for a different length of time, the results will provide potentially valuable insights into how quickly the intervention affects the primary outcome. As we will be training several clinicians at each site, we will use a mixed-effects design in which the clinician is a random effect and the group is a fixed effect. This approach will allow to analyse pooled information from all six groups while exploiting repeated measures by clinicians in each group. Furthermore, differences between patients’ socioeconomic position will be explored. In the absence of socioeconomic data in medical files, the patient’s address will be used to assign the level of social deprivation in their area of residence, based on Townsend’s definition of deprivation as a state of social disadvantage relative to the population average [36]. We will therefore geocode the patients’ address to find the corresponding IRIS, i.e. the smallest area for which socio-economic data are available comprising nearly 2000 inhabitants. More specifically, we will use an ecological deprivation level indicator, a French version of the European Deprivation Index (EDI) [37] which has been used in many studies to characterize the socioeconomic context and approximate individual socioeconomic position, including in cancer patients [38–40].

In parallel, an explanatory study will be carried out on French Health Insurance data to assess the feasibility of estimating annually a rate of access to fertility counselling and fertility preservation as a function of the age of the patients targeted in our trial: patients over 18 and under 40 years of age treated with chemotherapy for newly diagnosed breast cancer in the two French regions mentioned previously. Based on these results, we will be able to discuss the possibility of providing adaptable and cost-effective indicators for monitoring the impact of interventions to improve access to fertility preservation.

#### Analyses corresponding to objective 3

We will use the FIC model (“key Function, Implementation, Context”) developed in a previous project in our unit [26]. Originally, it was a model for clarifying and transferring interventions aimed at addressing and reducing social inequalities in health. The FIC model, highlighted the transferable theoretical elements (key functions) that underpinned activities implemented in a particular context, while considering the new context in which they may be implemented. Because our approach will consist of describing interventions in detail to understand what worked, how, in what context, to foster sustainable implementation across regions and networks, the model will be adapted to analyse our intervention in two regions. In addition, the model will document the conditions for its transferability to other regions and other types of cancer. To do so, we will support and implement a series of workshops, bringing together the stakeholders, field actors and researchers involved in the evaluation process, in a co-constructed way. Three workshops will be organized at the time of the design and at the end of the evaluation process. They will be deployed in the two regions, thought of as two contexts for the implementation of the same intervention. Around these workshops, we will mobilize multidisciplinary researchers competent in the field and useful to the process. The workshops, in the form of focus groups, will be organized face to face or using visio conference with each team.

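### The stated primary model has no patient covariate, and the protocol does not say whether the determinants of access that it names and collects will adjust the intervention estimate

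*Protocol article*

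**What the plan says.** The protocol article, under Analyses corresponding to objective 2, compares the counselling rate between the usual care and intervention phases. It states: "We will use linear regression models as appropriate for the primary outcome measure". On structure it adds: "we will use a mixed-effects design in which the clinician is a random effect and the group is a fixed effect". It lists no patient-level covariate and no calendar-time term.

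The Background reports, from regional work in Occitanie, that information and access were "influenced by the type of care structure, the woman’s age, her parity at the time of diagnosis, and the metastatic status of the cancer".

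Under Data collection: "we will collect patients’ age, date of diagnosis, cancer stage, and cancer center where the cancer has been diagnosed in the A-file". The treating centre is in file B. File E, taken from medical records, holds "number of children; address; presence or absence of information on fertility preservation; name of the oncologist".

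Under Secondary outcome measures, after listing age, stage, centre, chemotherapy, oncologist, number of children and address, the article says only: "These data will be analysed in relation with the primary outcome".

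**The concern.** The article goes far enough to fix the random and fixed structure of the primary model, yet it puts none of its own named determinants in that model. The one sentence on their use can be read in two ways. It may mean adjustment of the intervention effect, or a separate look at who gets counselling. Together with the words on using linear models as appropriate, this leaves the choice of covariates open until the data have been seen.

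The design makes this more than a formality. Only the order of six clusters is randomised. Women enter over 30 months, and within each group the intervention always follows usual care. There are no exclusion criteria, so metastatic and non-metastatic patients across the whole age range are included. Group fixed effects remove stable differences between groups. They do not remove a shift in age, parity or stage between the two phases of one group. Nor can group stand in for type of care structure, since 60 centres in 6 groups is about 10 centres per group.

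**Working it through.** **1. The plan's own precision figure.** The inputs are in the sample size section: "Assuming a proportion of access to fertility consultation of 23% before the intervention, with 6 clusters of about 120 patients and for an alpha risk". Alpha is set at 5%, power at 80%, and the stated detectable effect is 5.5 points. The schedule gives 7+10+13+16+19+22 = 87 usual-care and 87 intervention group-months, so the phases are about equal. For 750 women (375 per phase), a two-sided comparison of 23% with 32.1% has SE = √[(0.23×0.77 + 0.321×0.679)/375] = 0.0325, and (1.960+0.842)×0.0325 = 9.1 points. With 6×120 = 720 women the detectable effect is 9.3 points. One-sided, the figures are 8.1 and 8.2. The 5.5 points is not reproduced, but nothing below depends on it.

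**2. The text side by side.**

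| Determinant in the Background | Collected? | Term in the stated model? |
|---|---|---|
| Age | Yes, file A | No |
| Metastatic status | Derivable from stage, file A | No |
| Type of care structure | Not listed; derivable from the centre, files A and B | No; partly absorbed by clinician and group |
| Parity | Number of children, file E | No |

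**3. Precision.** If the covariates explain a share R² of the outcome variance left after group and clinician, the SE is multiplied by √(1−R²), and the equivalent sample is 750/(1−R²). The R² values are assumptions. The detectable effects (80% power, two-sided 5%) come from generalised least squares on the stated schedule, with group fixed, the transition month dropped, N = 750 and an assumed intracluster correlation of 0.01.

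| Assumed R² | SE multiplier | SE falls by | Equivalent N | Detectable effect, no period terms | Detectable effect, with period terms |
|---|---|---|---|---|---|
| 0 | 1 | – | 750 | 9.7 | 18.0 |
| 0.02 | 0.990 | 1.0% | 765 | 9.6 | 17.8 |
| 0.05 | 0.975 | 2.5% | 789 | 9.4 | 17.5 |
| 0.10 | 0.949 | 5.1% | 833 | 9.2 | 17.0 |
| 0.20 | 0.894 | 10.6% | 938 | 8.7 | 16.1 |

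**4. Drift common to all groups.** Number the months 0 to 29 and let c be a group's transition month. Usual care has mean month (c−1)/2 and the intervention phase (c+30)/2. The gap is 31/2 = 15.5 months, whatever c is. If changing case mix moves expected uptake linearly by x points from first to last month, a model with group effects but no time term is biased by (15.5/29)x = 0.53x. That is 1.1 points for x = 2 and 2.7 for x = 5 (assumed values). With period terms (the first 7 months, then 3-month steps) the least-squares bias is about 0.01x, with no patient covariate in the model.

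**5. What period terms leave.** A difference in case mix between phases that is particular to a group, or due to chance, shifts the unadjusted estimate by roughly the difference in the covariate's mean between phases times that covariate's effect on uptake. The documents give neither quantity, so this part cannot be sized.

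**6. Parity.** Number of children comes from medical records, and the intervention trains oncologists in fertility preservation. Its recording could improve after training, so missingness could depend on phase. Age and stage come from file A, which is queried directly, and carry no such risk.

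**The case against.** The strongest reply is that a condensed article commonly leaves the covariate list to the full protocol or the SAP, neither of which is shown. A reader might infer from the model description that adjustment is ruled out, or that the collected data will be analysed only in a separate exercise. The text supports neither reading. Nothing excludes adjustment, the sentence under Secondary outcome measures is compatible with it, and the phrase about linear models leaves room. What stands against the plan is narrower: it fixes the model's structure and does not commit to using the determinants it names.

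A reader might also infer that leaving these variables out is what exposes the trial to case-mix drift. Step 4 shows otherwise for drift shared by all groups: period terms remove it almost entirely. The four covariates would correct only its case-mix part and leave other secular trends untouched.

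Two further replies hold in part. An unadjusted primary estimate is a legitimate choice, and the gain at low R² would not change the trial's conclusion. Clinician and group effects already take up some of the care-structure signal, so the R² that counts is what the covariates add beyond them. Neither is a reason to forgo baseline predictors that are already in hand.

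**Conclusion.** The point holds as a modest one. The primary model is stated without patient covariates, and the protocol does not settle whether age, stage, centre and number of children adjust the intervention estimate, although it names age, parity, metastatic status and type of care structure as determinants of access. Adjustment would protect against chance or group-specific imbalance between phases (not sizeable from the documents). It would also lower the SE by about 1% to 5% for an assumed R² of 0.02 to 0.10, and by 10.6% at 0.20. It does not bring the detectable effect near 5.5 points, and it does not replace calendar-period terms. The R², the intracluster correlation and the drift sizes are assumptions.

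**What to change.** State that the primary intervention estimate is adjusted. Alongside calendar-period terms, pre-specify these fixed covariates:

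- age, continuous, from file A;
- metastatic versus non-metastatic stage, from file A;
- type of care structure, derived from the recorded centre, saying whether the diagnosing or the treating centre is used.

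Report the estimate without these covariates next to the adjusted one. Compare the completeness of number of children between phases first, and add it (0 versus 1 or more) to the primary model only if that comparison raises no concern. Otherwise use it in a sensitivity analysis. Do not rely on a missing-category indicator in the primary model. Reword the sentence under Secondary outcome measures so that adjustment and any separate analysis of determinants are distinguished.

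The cost is wording, plus a one-off classification of the 60 centres. No new patient data are needed.
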